## Abstract

**Introduction::**

Irritable bowel syndrome (IBS) is a common clinical label for medically unexplained gastrointestinal (GI) symptoms, recently described as a disturbance of the brain-gut-microbiota (BGM) axis. To gain a better understanding of the mechanisms underlying the poorly understood etiology of IBS, we have designed a multifaceted study that aim to stratify the complex interaction and dysfunction between the brain, the gut, and the microbiota in patients with IBS.

**Methods::**

Deep phenotyping data from patients with IBS (n = 100) and healthy age- (between 18 and 65) and gender-matched controls (n = 40) will be collected between May 2019 and December 2021. Psychometric tests, questionnaires, human biological tissue/samples (blood, faeces, saliva, and GI biopsies from antrum, duodenum, and sigmoid colon), assessment of gastric accommodation and emptying using transabdominal ultrasound, vagal activity, and functional and structural magnetic resonance imaging (MRI) of the brain, are included in the investigation of each participant. A subgroup of 60 patients with IBS-D will be further included in a 12-week low FODMAP dietary intervention-study to determine short and long-term effects of diet on GI symptoms, microbiota composition and functions, molecular GI signatures, cognitive, emotional and social functions, and structural and functional brain signatures. Deep machine learning, prediction tools, and big data analyses will be used for multivariate analyses allowing disease stratification and diagnostic biomarker detection.

**Discussion::**

To our knowledge, this is the first study to employ unsupervised machine learning techniques and incorporate systems-based interactions between the central and the peripheral components of the brain-gut-microbiota axis at the levels of the multiomics, microbiota profiles, and brain connectome of a cohort of 100 patients with IBS and matched controls; study long-term safety and efficacy of the low-FODMAP diet on changes in nutritional status, gut microbiota composition, and metabolites; and to investigate changes in the brain and gut connectome after 12 weeks strict low-FODMAP-diet in patients with IBS. However, there are also limitations to the study. As a restrictive diet, the low-FODMAP diet carries risks of nutritional inadequacy and may foster disordered eating patterns. Strict FODMAP restriction induces a potentially unfavourable gut microbiota, although the health effects are unknown.

**Trial registration number::**

NCT04296552 (ClinicalTrials.gov)

**Protocol version 1 May 2019**

## Introduction

1

Irritable bowel syndrome (IBS) is a symptom-based diagnosis characterized by chronic abdominal pain associated with altered bowel habits, in the form of diarrhea, constipation, or a mix between the two.^[1]^ IBS is the most common condition encountered by gastroenterologists, with a global pooled prevalence of 11.2%^[2]^ and a prevalence around 20% in the western world.^[3]^ In the absence of a structural or organic cause, growing evidence suggests that there is a plethora of factors that may elicit abnormal responses in patients with IBS. Collectively, these factors are described as dysregulation of the brain-gut-microbiota (BGM) interaction. As a bidirectional link between the brain and the gut, the axis reciprocally interacts with key sensorimotor functions, sympathetic and parasympathetic branches of the autonomic nervous system, the endocrine and immune system, the hypothalamic-pituitary-adrenal-axis, the enteric nervous system (ENS), and gut microbiota and metabolites. Alterations in gut microbiota composition or functions is known to impact human behaviour and brain physiology, and dysbiosis is commonly reported in patients with IBS.^[4,5]^ However, whether IBS-symptoms are caused by changes in microbiota still remains elusive and multiple pathways and mechanisms have been suggested to be involved. These include immune, endocrine, and neural signalling pathways, which the gut microbiota and metabolites may modulate. For instance, structural components of intestinal bacteria and bacterially produced metabolites [e.g., short chain fatty acids (SCFAs), tryptophan metabolites] may regulate immune function and cytokine production, with upstream effects on the blood–brain barrier or brain function through modulation of neuroinflammation. The gut microbiota, directly or through interactions with the host or diet, produce neuroactive compounds (gamma-aminobutyric acid, 5-hydroxytryptamine receptor, norepinephrine, etc) that may affect neuroendocrine functions locally or through humoral or neural routes such as signaling along the vagal nerve.^[6]^

Indeed, there is a substantial knowledge gap in regards to understanding pathophysiology in both the brain and the gut. The current view on disorders of the BGM axis has replaced the conventional focus on individual brain regions and cell types of the gut, integrating brain networks (brain connectome) and networks of gut cells and microbiota (gut connectome).^[7]^ In this study, we will employ cutting-edge omics and advanced computational methods to unravel gastrointestinal (GI) pathophysiology of IBS, link this information to results from multimodal brain imaging examination, gastric accommodation test, and information from psychometric tests and questionnaires, and translate these into clinical biomarkers. By this, we aim to stratify the diagnosis and improve treatment for patients with IBS.

## Methods/Design

2

### Objectives

2.1

The primary objective of this study is to increase knowledge and understanding of BGM axis dysfunction and identify covariance across multiple phenotypes leading to identification of biomarkers.

The secondary objectives are addressing the multifaceted manifestations of BGM axis dysfunction, specifically

To identify and quantify structural and functional brain connectivity signatures, including visceral pain provocation and psychophysiological measures, using advanced neuroimaging techniques and statistical approaches.To investigate clinical biochemistry in blood (plasma, serum).To evaluate upper GI motility patterns using transabdominal ultrasound.To investigate GI biopsies for multi-omics analysis and complex molecular subclassification.To identify microbiota signatures and metabolites associated with gut-brain equilibrium or dysfunction in IBS patients and healthy controls.To investigate clinical effects of short and long-term strict low-FODMAP diet.To examine and compare the compositional and functional response of gut microbiota at baseline and after the low-FODMAP-dietary intervention, and the relationship with clinical and psychophysiological outcomes.To evaluate if the GA-map technology can be used to predict the response to treatment (to distinguish responder and non-responders prior to low-FODMAP diet).To investigate cognitive and emotional function associated with brain structures and functions known to be affected in adults with IBS, and personality traits and behaviour expected to be of importance to the patient's everyday functioning and effects of a strict low-FODMAP diet.To define phenotypes and biomarkers from all our abovementioned data using high dimensional data-driven and machine learning techniques.

### Study population, recruitment, and consent

2.2

Eligible patients from the Bergen area are recruited from the IBS outpatient clinic at Haukeland University Hospital and through social media. Patients are informed about the study online (www.braingut.no.) and are individually informed by telephone by a study nurse, before inclusion. If a patient decides to participate in the study, (s)he signs an informed consent. Patient recruitment will take place between May 2019 and December 2021. Inclusion criteria for the studyincluded age between 18 and 65 years; fulfillment of the Rome-IV criteria for IBS: Reports of recurrent abdominal pain on average at least 1 day per week during the previous 3 months that is associated with alterations in bowel habits; duration at least 6 months and an IBS-symptom severity score (SSS) >175.^[8]^ Exclusion criteria for the study included pharmacological treatment affecting the GI-tract, including treatment for depression; presence of an organic disease such as coeliac disease, inflammatory bowel disease, diabetes, active *Helicobacter pylori* infection, polycystic ovary syndrome, and neurological diseases such as multiple sclerosis, Parkinson's disease, and amyotrophic lateral sclerosis; treated with systemic antibiotics within the last 3 months; probiotics or low-FODMAP-diet within the last 3 weeks or being vegan or vegetarian; regular use of analgesics; pregnancy; previous intestinal surgery except appendectomy; claustrophobia or having metallic implants that are not MRI compatible; been travelling outside Europe within the last 3 weeks (or plan to travel in the nearest future); participation in any other simultaneous clinical study; inability to comprehend and respond to questionnaires or follow dietary guidance.

Three patients and one healthy volunteer will be included in the study every 4 weeks until the necessary number of participants have been enrolled (IBS n = 100 patients, HC n = 40) at baseline. Sixty candidates with IBS-D will enroll in the 12-week strict low-FODMAP dietary intervention. Additional patients will be enrolled to replace patients who drop out during baseline until the end of the inclusion period. Patients who unexpectedly get claustrophobic during brain scanning may be included in the dietary intervention without functional magnetic resonance imaging (fMRI) examination.

### Study design

2.3

The study is an open, single-center, case–control characterization study, followed by open label dietary intervention for a subgroup of subjects with IBS-D. Table 1 gives an overview of the study procedures and events during case–control characterization (baseline) and the following 12-week strict low-FODMAP diet intervention.

**Table 1 T1:**
[figure not shown]
Brain-gut study procedures and events during baseline and 12-week strict low-FODMAP diet intervention.

## Outcomes

3

### Primary outcome

3.1

Primary outcomes included proportion of patients with treatment success in the lowFODMAP dietary intervention. Treatment success is defined as an improvement of ≥50 points on the IBS symptom severity score (IBS-SSS) at 12 weeks after treatment start compared with the score at baseline.

### Secondary outcomes

3.2

≥50 points decrease in the IBS symptom severity score (IBS-SSS) from the scores 4 weeks after treatment compared to baseline.≥13 points increase in the IBS-Qualiy of Life (IBS-QoL) week 4 and/or week 12 after treatment when compared to the scores at baselineTwenty percent reduction on visual analog scale on nausea, pain, and bloating measured post lactulose-test at week 12, compared with baseline scores.Proportion of patients with change dysbiosis index at week 4 and week 12 according GA-map technology, compared with baseline and/or healthy controls.

### Explorative outcomes

3.3

Changes in structural and functional brain connectivity signatures, including visceral pain provocation and psychophysiological measures at 12 weeks compared with baseline, and healthy controls.Changes in resting state regional brain interactions at 12 weeks compared with baseline and healthy controls, as measured with fMRI.Changes in cortical thickness (FA values) as measured with DTI (MRI)Differences in taxonomy and function of the microbiome, the immune system, metabolome and gut epithelial barrier in IBS patients at 12 weeks compared with baseline measures, and healthy controls.Changes in levels of SCFA composition, compared with baseline, and heathy controls.Changes in cognitive and emotional function, personality traits, and behavior at 12 weeks compared with baseline, and healthy controls.Improvements in The Conner's Continuous Performance Test (CPT-3) at 12 weeks in IBS patients, compared with baseline.

### Sample size estimation

3.4

Generally, for samples size calculation and statistical power, we would make the following assumptions: Anticipated effect size (f^2^) is medium (0.20), desired statistical power level is 0.8 (80%) with type-I error of 5% (α = 0.05). On the basis of these assumptions, the minimum required samples size is 59 in each group for multiple regression analyses. Previous experience with this patient group has shown that we may expect a high level of missing data. To allow diagnostic subclassification, we therefore have increased the baseline sample size to n = 100, and the dietary intervention samples size n = 60 in patients with IBS-D and n = 40 for healthy controls. However, to identify biomarkers and patient subpopulations, comprehensive analysis methods will be employed to combine neuroimaging and neuromics data with clinical patient data. Although IBS is a highly heterogeneous patient group, we believe machine learning techniques and possibly pre-trained models will enable us to make inferences about an IBS population from the given sample, considering the limitation of cost, time, and convenience of data collection.

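### Section 3.4 sets a minimum of 59 per group for 80% power, but enrols 40 controls and a diet group with a margin of one, although much missing data is expected

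*Protocol article*

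**What the plan says.** The Sample size estimation section (3.4) gives the assumptions "Anticipated effect size (f^2^) is medium (0.20" and "desired statistical power level is 0.8 (80%) with type-I error of 5% (α = 0.05", and concludes that "the minimum required samples size is 59 in each group for multiple regression analyses". It does not state the number of predictors.

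The next sentence reads "Previous experience with this patient group has shown that we may expect a high level of missing data". No rate is attached. The section goes on to say "we therefore have increased the baseline sample size to n = 100", followed in the same sentence by "the dietary intervention samples size n = 60 in patients with IBS-D and n = 40 for healthy controls".

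The Abstract and section 2.2 repeat 100, 60 and 40, so 40 is not a misprint. Section 2.2 provides for replacing patients who drop out during baseline. It states no replacement for losses in the diet phase or among controls, and it lets patients who become claustrophobic enter the diet phase without fMRI. Sections 3.2 and 3.3 use healthy controls as a comparator for several secondary and explorative outcomes.

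**The concern.** The stated requirement and the enrolled numbers sit a sentence apart and do not agree. Against a minimum of 59 per group, only the baseline IBS group carries a real reserve. The diet group is the minimum plus one, and the control group is about a third below it (19/59 = 32%). The sentence that lists these sizes opens by presenting an increase made in response to expected missing data, so a reader may take 60 and 40 as sizes with an allowance built in.

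The per-group label is also doubtful in itself. A multiple-regression sample size is normally the total number of observations in one model, and 59 can be reproduced as exactly that.

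At stake is how null results are read. Section 3.4 gives one 80% figure for regression analyses in general. A null finding within the diet group, or between diet patients and controls, could be taken as adequately powered when the section's own assumptions do not support that.

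**Working it through.** **Inputs from section 3.4.** f² = 0.20; α = 0.05; target power 0.80; stated minimum 59; enrolled 100 IBS patients at baseline, 60 IBS-D patients in the diet phase and 40 controls.

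**Inputs not given, so assumed.** The number of tested predictors u (range 1 to 5 tried) and the missing-data rate (10% and 20% shown).

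**Reproducing 59.** F test of a multiple regression with noncentrality λ = f² × N and degrees of freedom u and N − u − 1. Smallest N reaching 80% power:

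| u | 1 | 2 | 3 | 4 | 5 |
|---|---|---|---|---|---|
| N | 42 | 52 | **59** | 65 | 70 |

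Only u = 3 gives 59 (λ = 0.20 × 59 = 11.8; df 3 and 55; power 0.803). This N is the total for one model. It does not fix the model size: testing three coefficients in a model with anywhere from 3 to 8 predictors also needs 59.

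**Reading A: 59 is needed within each group (u = 3, f² = 0.20).**

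| Group | Evaluable N | Power |
|---|---|---|
| Baseline IBS, complete | 100 | 0.97 |
| Diet, complete | 60 | 0.811 |
| Diet, one missing | 59 | 0.803 |
| Diet, two missing | 58 | 0.795 |
| Diet, 10% missing (60 × 0.90) | 54 | 0.76 |
| Diet, 20% missing (60 × 0.80) | 48 | 0.70 |
| Controls, complete | 40 | 0.60 |

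The result at N = 40 depends on the unstated u: 0.79, 0.68, 0.60 and 0.54 for u = 1, 2, 3 and 4. At u = 3, 80% power needs f² of about 0.30 at N = 40 and about 0.25 at N = 48. The 100 baseline patients still leave 59 evaluable with 41% missing (100 × 0.59 = 59).

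**Reading B: 59 is the total N of one regression pooling patients and controls (u = 3, f² = 0.20).**

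| Pooled sample | N | Power |
|---|---|---|
| 100 + 40 | 140 | 0.996 |
| 60 + 40 | 100 | 0.97 |
| 48 + 32 (20% missing in both) | 80 | 0.92 |

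Here the sizes are ample and the per-group label is the error.

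**Simple two-group comparison, as a yardstick.** Two-sided t test with noncentrality d × √(n₁n₂/(n₁ + n₂)). With 59 v 59, d = 0.52 is detected with 80% power. At that d:

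| Comparison | Power | d for 80% power |
|---|---|---|
| 100 v 40 | 0.79 | 0.53 |
| 60 v 40 | 0.71 | 0.58 |
| 48 v 40 (20% missing, patients only) | 0.67 | 0.61 |
| 48 v 32 (20% missing in both) | 0.61 | 0.65 |

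**The case against.** The strongest reply is that the two criticisms cannot both hold. If 59 is a total, 40 controls breach nothing. If 59 is per group, the label is legitimate. This stands, and the point is therefore put as an either/or: on each reading a different part of section 3.4 is wrong.

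A reader might infer that the trial as a whole does not deliver 80% power. The article does not support that. Pooled regressions keep at least 0.92 in the cases above, the baseline IBS group has ample reserve, and a complete 100 v 40 comparison loses about one percentage point. The 0.60 figure applies to a regression within controls alone, which the article does not describe.

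A reader might also infer that the calculation was for a model with three predictors. That is unproven, since models with up to eight predictors and three tested coefficients give the same N.

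Two further replies have weight. The d = 0.52 yardstick is not in the article, which speaks only of f² and regression. The expected missing data is described for patients, so applying losses to controls is an added assumption. The wording can also be read as increasing only the baseline group, with 60 and 40 simply listed after it. On that reading, though, the diet group still has no stated allowance for the losses expected.

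Finally, the primary outcome is a responder proportion among diet patients and does not use controls, and much of the study is exploratory. That lowers the severity but does not reconcile the numbers.

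**Conclusion.** The point holds in this limited form and should be fixed. Section 3.4 states a requirement that its own enrolled numbers do not meet as written. On the per-group reading, controls fall 19 short, and the diet group keeps 80% power only while no more than one case is missing, falling to about 0.76 at 10% and 0.70 at 20% missing. On the total-N reading, the per-group wording is wrong and pooled analyses are well powered. A plain comparison of 60 diet patients with 40 controls has 0.71 power at the effect that 59 v 59 would detect with 80%.

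These figures rest on three tested predictors, inferred from 59, and on assumed missing rates. The arithmetic behind 59 is sound.

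**What to change.** Reword section 3.4 so that it:

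1. says whether 59 is a per-group number or the total N of one regression, and gives the number of predictors (tested and in the model) behind it;
2. names an assumed missing-data rate for patients and for controls;
3. limits the 80% claim to the analyses that meet it after that rate is applied;
4. restates power or the detectable effect at the enrolled sizes for the rest. With three tested predictors, examples are f² of about 0.30 for a regression within 40 and about 0.25 with 48 evaluable diet patients; for a two-group comparison, d of about 0.58 for 60 v 40;
5. does not present 60 and 40 as sizes that absorb missing data.

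The cost is rewriting one section and a less favourable stated power. No extra participants are needed.

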### Clinical assessment

3.5

#### Structural and functional brain MRI

3.5.1

Participants will be scanned using a Siemens Biograph mMR PET/MRI, incorporating a 3 T MRI Verio scanner with MQ gradients (45 mT/m @200 T/m/s), a 12-channel RF head coil and paralell imaging. The following MRI sequences will be applied: Scout (136 images, voxelsize 1.6 x 1.6 x 1.6 mm^3^; iPAT = 3; TA 0:14); T1-w 3D MPRAGE (192 slices, voxelsize 1.0 x 1.0 x 1.0 mm^3^; TR/TE/TI = 2400/2.26/900 ms, FA = 8 deg; iPAT = 2; TA_5:35), T2-w 3D TSE (192 slices; voxelsize 1.0 x 1.0 x 1.0 mm^3^; TR/TE = 3200/407 ms, FA = 120 deg; iPAT = 2; TA 5:12), GRE field map (36 slices, voxelsize 3.0 x 3.0 x 3.75 mm^3^; TR/TE1/TE2 = 400/4.92/7.38 ms, FA = 60 deg; iPAT = 1; TA 0:54); rs-fMRI epi2d moco (47 slices, voxelsize 2.4 x 2.4 x 3.12 mm^3^, 200 vols; TR/TE = 2890/30 ms, FA = 90 deg; iPAT = 2; TA 9:48), rs-fMRI epi2d moco (32 slices, voxelsize 2.4 x 2.4 x 3.12 mm^3^, 200 vols; TR/TE = 1980/30 ms, FA = 90 deg; iPAT = 2; TA 6:43), dMRI MMDW (47 slices, voxelsize 2.4 x 2.4 x 3.12 mm^3^;TR/TE = 8000/113 ms, FA = 90 deg; iPAT = 2; diff.scheme = bipolar; phase encoding A<
>A; bvals = 0; TA 0:30. Total examination time ∼45 min.

Functional MRI, using blood-oxygenation-level dependent (BOLD) contrast, will be used to record neuronal activity (i.e., neurovascular responses) in both IBS patients and healthy controls. Resting-state fMRI is a special “task-free” variant in which the subject is asked to lie as still as possible in the head coil while being continuously scanned, to investigate spontaneous brain activity (resting state networks).^[9–12]^ Diffusion imaging (dMRI) involves measuring of water diffusion in brain tissue. This provides information on a voxel-by-voxel basis about white matter microstructure, properties of with matter fiber bundles in the brain.^[13–15]^ For this study, we do not plan to use the opportunity of truly simultaneous acquisition of structural and functional information of the same brain regions from both MRI and PET. Our cerebral MRI protocol is a partly compliant with and motivated by the standardized Pain and Interoception Imaging Network protocol.^[16]^

#### Psychometric testing

3.5.2

The Repeatable Battery for the Assessment of Neuropsychological Status (RBANS) is a brief, individually administered test-battery designed as a screening instrument to evaluate neuropsychological status of adults, ages 20 to 89 years.^[17]^ The test battery includes 12 subtests giving measures of attention, language, visuospatial/constructional abilities, and immediate and delayed memory function, in addition to a composite score and estimates of intellectual function according to available Scandinavian norms. In the present study, the results will be used for defining the cognitive function of the participants, as a covariate in the statistical analyses, and for establishing norms for patients with IBS.

The Behavior Rating Inventory of Executive Function (BRIEF-A) will be used to assess executive functions (EFs), as they are experienced in the daily life of the participants.^[18]^ The scale includes 86 items in 8 clinical scales (Inhibit, Shift, Emotional Control, Initiate, Working Memory, Plan/Organize, Organization of Materials, Monitor) and 2 validity scales (Inconsistency and Negativity). These scales form 2 global indexes (Behavioral Regulation, Metacognition, Global Executive Composite score) representing overall EF.

The Conners’ Continous Performance Test – third edition (CPT-3) is a computerized test wherein the participants are instructed to push the spacebar as soon as a target appears on the screen (a letter), except when the letter is X.^[19]^ The test is characterized by high signal-to-noise ratio by including 90% target stimuli and 10% no-target stimuli (x). The test incudes 360 trials presented across 6 blocks, with 3 subgroups with different interstimulus intervals. The test durance is 14 minutes, and the results generate measures of reaction time, accuracy, variability, consistency, and vigilance. BRIEF and CPT-3 will be used as a measure of attention and EF in patients with IBS, as a predictor of treatment response (baseline); and as an outcome variable (change from baseline to follow-up).

The NEO-FFI-3 is a 60-item version of the NEO-PI-3 providing a quick and reliable measure of the Five-Factor model of personality (Neuroticism, Extraversion, Openness, Agreeableness, and Conscientiousness).^[20,21]^ The instrument is well validated for use in several countries. Measures will include the 5 factors as well as profiles of factors for individual adults. In the present study, the personality assessment will be part of the phenotyping of adults with IBS and controls; one of the predictors of treatment response, a more general predictor of quality of life, pain, and other self-reported challenges associated with IBS, and related to the BGM axis.

